### Objectives and endpoints

Primary objective is the evaluation of seizure activity during a course of radiotherapy for high-grade gliomas. Progression of seizure activity during the course of radiotherapy compared to baseline is defined as increase of frequency of seizures by more than 50%, increase of severity of seizures (i.e. increase of generalized seizures by more than 50%), or increase of the dose of anti-epileptic medication by at least 25% or initiation of anti-epileptic medication. The latter criterion was defined in accordance with another situation in radiation oncology, radiotherapy of painful bone metastases [10]. These parameters will be assessed using a seizure diary kept by the patients during the course of radiotherapy. In addition, seizure frequency up to 6 weeks following radiotherapy (seizure diary), patient satisfaction with the seizure diary, and electroencephalography (EEG) activity typical for epilepsy will be evaluated.

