### Eligibility criteria

Inclusion criteria include histologically proven newly diagnosed or recurrent grade III or IV glioma (associated or not associated with seizures), indication for normo-fractionated radiotherapy, Eastern Cooperative Oncology Group performance score 0–2, age ≥ 18 years, written informed consent (taken by physicians registered as investigators for this trial), and capacity of the patient to cooperate (including the use of a seizure diary). Exclusion criteria include pregnancy/lactation and limited legal capacity or being under legal supervision.

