**Fig. 1 Fig1:**
[figure not shown]
Timeline of enrolment, interventions and assessments of the SURF-ROGG trial

The patients keep a seizure diary during radiotherapy and up to 6 weeks following radiotherapy. Every day, the patients document the number and type of seizures and intake of anti-epileptic medication. At the end of radiotherapy, the patients are asked to complete a questionnaire regarding their satisfaction with the seizure diary.
2.Objective assessment of seizure activity

To obtain an objective assessment of seizure activity in addition to patient reported outcomes, an EEG is performed during the first and sixth week of radiotherapy, and during the sixth week following radiotherapy.
3.Adverse Events

Adverse events other than seizures will be assessed on an ongoing basis according to CTCAE v5.0 [11].

In addition, potential prognostic factors regarding the increase of seizure activity during the course of radiotherapy will be evaluated including seizure activity at baseline, age, gender, glioma grade, recurrent glioma, isocitrate dehydrogenase (IDH1/2) mutation status, methylation of the O^6^-methylguanine-DNA methyl-transferase (MGMT) gene promoter, tumor site, tumor size, cortical involvement and extent of upfront surgery.

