## Statistical methods for investigated endpoints

The focus of the statistical analysis is descriptive and exploratory in nature. If statistical tests are applied, they are to be interpreted on an exploratory perspective. All data recorded in the case report forms describing the study population (demographic and clinical characteristics, at baseline) will be analyzed descriptively. Categorical data will be presented in tables with frequencies and percentages. Continuous data will be summarized with at least the following: Frequency (n), median, quartiles, mean, standard deviation (standard error), minimum and maximum. Number of patients with protocol deviations during the study and listings describing the deviations will be provided. The seizure frequency at baseline and during the course of radiotherapy will be calculated by summing the number of seizures in each period and dividing by the total duration (days), excluding days with no available diary data, and multiplying by 7 to normalize to a weekly rate. The resulting normalized frequencies form the basis for calculating the composite primary endpoint. The point estimate of the rate of progressors and the associated 95% confidence interval will be presented. To test whether the rate of progressions is significantly increased beyond 10%, the one-sided binomial test at a one-sided 2.5% significance level will be applied.

Furthermore, a logistic regression model including baseline seizure including seizure activity at baseline, age (≤59 vs. ≥60 years), gender, glioma grade (grade III vs. IV), recurrent glioma (no vs. yes), IDH1/2 mutation status (mutation vs. wild type), methylation of the MGMT gene promoter (yes vs. no), tumor site (frontal vs. temporal vs. parietal vs. other sites), tumor size (≤ median vs. > median), cortical involvement (yes vs. no) and extent of surgery (no resection/biopsy only vs. subtotal resection vs. gross total resection) will be fitted to identify potentially relevant prognostic factors [14].

Adjusted odds ratios and 95% confidence interval (Wald χ2) will be derived. In addition, each component of the primary composite endpoint will be subjected to a separate statistical analysis using the same methods described above. For exploratory purposes, the analyses described above will also be conducted by focusing on the seizures classified as generalized and generalized/grand mal only.

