## Discussion

Primary brain tumors such as gliomas can be associated with seizures. For patients with grade III or IV gliomas, pre-treatment seizure rates of 29–67% and 9–45%, respectively, were reported [3, 15–19]. Moreover, in a study from our group, the prevalence of seizures prior to radiotherapy was 48.8% in patients with grade III gliomas and 21.5% in patients with grade IV gliomas, respectively [14].

Radiotherapy improves long-term seizure outcomes in glioma patients. In a retrospective study of 43 patients with diffuse gliomas (33 patients with a grade II glioma and 10 patients with a grade III glioma), seizure reduction of ≥50% compared to baseline was observed in 31 patients (72%) at 3 months following radiotherapy [20]. Moreover, in a randomized trial comparing early radiotherapy with 54 Gy in 30 fractions to radiotherapy performed only at the time of progression, seizure control at 1 year was better in the early radiotherapy group [21]. However, during the course of radiotherapy, seizures may occur for the first time or the frequency of seizures may increase, because radiotherapy leads to an acute inflammatory reaction, which can be associated with edema and increased intracranial pressure [8, 9]. In 2004, Bhansali et al. reported 11 patients with radiation-induced brain disorders [8]. Four of these patients (36%) had developed generalized seizures. In a review article published in 2007, seizures were reported to be symptoms of both acute radiation encephalopathy and late radiation-related necrosis [9]. However, no study has been available so far that evaluated the effect of irradiation to the brain on seizure activity during the course of radiotherapy for high-grade gliomas. However, these data would be very important in order to improve the monitoring and, if required, the anti-epileptic treatment of these patients. Therefore, the SURF-ROGG trial has been designed that will evaluate the seizure frequency during a course of radiotherapy for high-grade (grade III or IV) gliomas. Patients with low-grade (grade I or II) gliomas will not be included, because the treatment of these tumors and the dose-fractionation of radiotherapy are almost always different from the treatment of high-grade tumors [12].

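### Baseline seizure activity is a candidate prognostic factor for an outcome defined relative to that same baseline, so its odds ratio cannot be read as prognosis

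*Protocol article*

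**What the plan says.** In the protocol article, Objectives and endpoints sets the outcome: "Progression of seizure activity during the course of radiotherapy compared to baseline is defined as increase of frequency of seizures by more than 50" percent, or generalized seizures up by the same margin, or "increase of the dose of anti-epileptic medication by at least 25% or initiation of anti-epileptic medication".

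Statistical methods for investigated endpoints derives weekly seizure rates at baseline and during radiotherapy and adds: "The resulting normalized frequencies form the basis for calculating the composite primary endpoint". It then plans "a logistic regression model including baseline seizure including seizure activity at baseline" and ten further factors. This model "will be fitted to identify potentially relevant prognostic factors", with adjusted odds ratios and Wald intervals. The same methods are to be repeated for each component of the composite and for generalized seizures only.

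Assessments confirms the target: "potential prognostic factors regarding the increase of seizure activity during the course of radiotherapy will be evaluated including seizure activity at baseline".

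Eligibility criteria admits gliomas "associated or not associated with seizures", so zero baselines will occur. The article does not state how baseline seizure activity is coded or how long the baseline window is. The full protocol or analysis plan may do so.

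**The concern.** One count, measured with error, serves twice: as the reference that the outcome must exceed and as a predictor of that outcome. A patient whose baseline count was low by chance needs few seizures to exceed +50%, and one whose count was high by chance needs many. Part of any association between baseline and progression is therefore built in (mathematical coupling and regression to the mean), whatever radiotherapy does. If baseline is coded as any versus none, the odds ratio compares two different events, worsening and new onset.

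Baseline seizure activity is the first factor on the list and an obvious one to consult when asking whom to watch. The study's declared aim includes generating hypotheses, and its Discussion expects the findings to contribute to closer monitoring. A coefficient whose no-effect value is unknown is a poor source of hypotheses.

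**Working it through.** **The plan's own figures.** The article gives no figure for the logistic model. Its sample size figures reproduce and do not involve this covariate. With n = 32 and a null rate of 10%, the exact test rejects at 8 or more progressors (one-sided alpha 0.0117), and its power at 30% is 0.788 against the stated 80%. With a null rate of 5%, it rejects at 5 or more and power is 0.981 against the stated 98%.

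**The coupling by hand.** Assume a 4-week baseline and a 6-week course. With baseline count b, frequency progression needs a radiotherapy count F with F/6 > 1.5 × b/4, that is F > 2.25b. Take patients who all have the same unchanging true rate of 0.5 per week, so F is Poisson with mean 3:

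- b = 1: F ≥ 3, probability 1 − e⁻³(1 + 3 + 4.5) = 0.58
- b = 2: F ≥ 5, probability 1 − e⁻³(1 + 3 + 4.5 + 4.5 + 3.375) = 0.18
- b = 3: F ≥ 7, probability 1 − e⁻³(16.375 + 2.025 + 1.0125) = 0.03

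These patients have identical prognosis and no treatment effect, yet the chance of progression falls from 58% to 3% with the baseline count.

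**Simulation with no radiotherapy effect, patients with at least one baseline seizure.** Assumptions, none of them in the article: each patient has a constant rate drawn from a gamma distribution (mean 0.5 to 2 per week, shape 1 to 3), counts are Poisson, the baseline lasts 4 or 6 weeks and the course 6 weeks.

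- The >50% criterion is met by chance in 27 to 36% of patients at or below the median baseline and in 5 to 10% above it: odds ratio about 0.11 to 0.29.
- Per doubling of baseline, the odds ratio is 0.31 to 0.53.
- With 10% of patients progressing on medication for unrelated reasons, high versus low gives about 0.26 to 0.44. Under wider assumptions (shape down to 0.5, a 1-week baseline allowed) it runs from 0.33 to 0.63.
- For any seizure during radiotherapy, the odds ratio per doubling is 2.1 to 4.3, the opposite direction.

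**All eligible patients.** The Discussion reports that "the prevalence of seizures prior to radiotherapy was 48.8% in patients with grade III gliomas and 21.5% in patients with grade IV gliomas". So 100 − 48.8 = 51.2% to 100 − 21.5 = 78.5% had none. That is only a guide to the share of patients who will never seize, which was varied from 0 to 70%. Shape was 0.5 or 1. Any seizure from a zero baseline counts as progression, on frequency alone. Odds ratios with no radiotherapy effect:

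| Never-seizers | Baseline window | Any vs none | High vs rest |
|---|---|---|---|
| 0% | 1, 4 or 6 weeks | 0.03 to 0.58 | 0.008 to 0.27 |
| 50% | 1 week | 0.16 to 0.85 | 0.03 to 0.24 |
| 50% | 4 to 6 weeks | 1.7 to 5.6 | 0.54 to 0.82 |
| 70% | 4 to 6 weeks | 3.8 to 12.8 | 1.06 to 1.49 |

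If patients with a zero baseline cannot count as frequency progressors, any versus none is infinite on frequency alone and 1.5 to 3.7 with 10% medication progression.

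**The case against.** A reader might infer that a high baseline will always look strongly protective, and that the model would therefore label patients with many seizures as low risk. The documents do not support that. The model is not restricted to patients with baseline seizures, and the cited prevalences imply that roughly 0.215 × 32 = 7 to 0.488 × 32 = 16 of the 32 analysed patients would have had any before radiotherapy. Truly seizure-free patients rarely progress, which pulls the association the other way and can reverse it. This part of the objection stands and limits the point to what is stated here.

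The medication component is not computed from seizure counts, and weekly discussion with a neurologist may make it common. It dilutes the artefact in the composite. In the simulations dilution did not remove it, and the separate frequency and severity models have no such dilution.

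The analysis is labelled exploratory, and the primary test does not use the covariate. At the assumed 30% rate there are 0.30 × 32 = 9.6, about 10, events for about 14 regression parameters, so the estimate will be unstable anyway. This limits the consequence. However, an exploratory label guards against over-reading p-values and does not move the no-effect value back to 1.

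Conditioning on baseline is not in itself an error. Baseline seizures differ by grade (48.8% versus 21.5%), so dropping the covariate would cost the other factors that adjustment. This stands and argues against removal.

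Coding and zero handling may be fixed in the full protocol or analysis plan. That would settle the direction of the artefact, but a coding choice would not generally remove it.

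**Conclusion.** The point holds in a limited form. Because the baseline rate is both the reference for two of the three progression components and a candidate predictor, its odds ratio has no known no-effect value and cannot be read as prognosis. Among patients with baseline seizures the artefact is protective and large. Across the whole eligible population its direction is not fixed, and simulated no-effect values lie both far below and far above 1. A uniform protective bias should not be claimed.

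The sizes rest on assumed rates, between-patient variation, baseline windows and never-seizer shares. The coupling itself follows from the definitions in the article. The matter is secondary: it affects one exploratory coefficient, repeated in the component models, and leaves the primary test and the estimated progression rate untouched.

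**What to change.** In Statistical methods for investigated endpoints:

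1. Keep baseline seizure activity in the logistic models as an adjustment variable only. State that its odds ratio is not interpreted as prognostic for the composite, frequency or severity outcomes.
2. Add one exploratory model for its prognostic association, with an outcome that does not contain baseline. This can be any seizure during radiotherapy (yes/no), or the seizure count during radiotherapy in a negative binomial model with the log of recorded diary days as offset and baseline rate as covariate.

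The cost is a change of wording and one extra exploratory model. No new data are needed, because the diary already yields both outcomes and the plan already reports the rate of any seizure per interval. The downside is that the baseline factor is reported on a different outcome scale from the other factors.

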## Sample size calculations

The main goal of the study is to generate objective data on the occurrence, frequency and severity of seizures and the use of anti-epileptic medication during the course of radiotherapy applying standardized questionnaires, in order to evaluate the potential effect of radiotherapy in patients with high-grade gliomas and generate hypotheses. Thirty-two patients are required for the statistical analyses. Assuming that 10% of patients do not fulfil these requirements, a total of 35 patients should be enrolled to this trial. With this sample size, a one-sample binomial test with a one-sided significance level of 2.5% has a power of 80% to yield statistical significance if the rate of patients with progression of seizure events during the course of radiotherapy is 30% (rate under the alternative hypothesis), assuming a ‘natural’ background progression-rate of 10% without radiotherapy (null hypothesis). The latter rate was chosen after discussions with experienced neurologists. If the natural course of the disease would lead to a progression-rate of 5% without radiotherapy, the power increases to 98%. Recruitment should be completed within 12 months. The radiotherapy period is 6–6.5 weeks, and follow up is 6 weeks. Thus, duration of the trial is about 15 months.

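### Age and tumor size enter the exploratory prognostic model as two groups each, which discards information at no saving in parameters and ties the size odds ratio to this sample's median

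*Protocol article*

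**What the plan says.** The section on statistical methods for investigated endpoints plans one logistic regression with eleven factors, which "will be fitted to identify potentially relevant prognostic factors". Among them are age, coded as "age (≤59 vs. ≥60 years", and tumor size, coded as "tumor size (≤ median vs. > median". Adjusted odds ratios with Wald intervals are to be reported, and the same methods are repeated for each component of the composite endpoint.

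The article gives no reason for either cut beyond a citation attached to the model, and it mentions no continuous version. No value in cm or ml is given for the size median, so it can only be the median of the patients in this trial. The age cut is a fixed value.

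The same section states the status of the work: "The focus of the statistical analysis is descriptive and exploratory in nature". The sample size section gives the numbers that bear on the model: "Thirty-two patients are required for the statistical analyses", and the progression rate on which power is computed "is 30% (rate under the alternative hypothesis".

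**The concern.** Both factors are available as measurements. Age is recorded before radiotherapy, and a median split of size needs the measured sizes. Cutting them treats patients aged 59 and 60 as different and patients aged 60 and 80 as alike. If risk changes gradually with age or size, part of the information is discarded. No parameter is saved in return, because a two-group term and a linear term each use one degree of freedom.

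The size cut has a second drawback. Its odds ratio compares patients above and below a threshold that is unknown until the data are in, and that would differ in another cohort. The article hopes to generate hypotheses and lead to a larger prospective trial, and such a contrast carries over poorly.

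At stake is how well an exploratory model can do its one stated job, which is to pick out prognostic factors.

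**Working it through.** **The plan's own figure.** The documents state no figure for information kept or lost by the cuts. The related figure is the power statement that supplies the number of patients and the event rate. With 32 patients, 10% under the null, 30% under the alternative and one-sided 2.5%, the exact binomial test rejects at 8 or more progressors. Its exact alpha is 0.0117 and its power 78.8%, against 80% stated. With a 5% background rate it rejects at 5 or more, and power is 98.1%, against 98% stated. The inputs are therefore taken as given.

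**Information kept by a cut.** For a factor with a small linear effect on the logit, the share kept is the squared correlation between the factor and its two-group indicator. Let q be the proportion below the cut, z the standard normal quantile of q, and φ the standard normal density.

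- Normal factor: share kept = φ(z)² / [q(1 − q)]
- Uniform factor: share kept = 3q(1 − q)

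The documents give no mean, SD or median for age or size, so the distributions below are assumptions.

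| Assumed factor and cut | Calculation | Loss |
|---|---|---|
| Normal, cut at median | 1 − 2/π = 1 − 0.637 | 36% |
| Uniform, cut at median | 1 − 3 × 0.5 × 0.5 | 25% |
| Uniform, 30/70 split | 1 − 3 × 0.3 × 0.7 | 37% |
| Normal age, mean 60, cut at 60 | as the median split | 36% |
| Normal age, mean 55 or 65, SD 10 to 15 | normal formula | 39–42% |
| Normal age, mean 50, SD 15 | z = 0.67, q = 0.75 | 46% |
| Normal age, mean 50, SD 10 | z = 1, q = 0.84: 1 − 0.242²/(0.84 × 0.16) | 56% |
| Size right-skewed (exponential or lognormal), effect linear in raw size, median split | simulated | 48–63% |
| Size lognormal, effect linear in log size, median split | as normal | 36% |

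**How far the size threshold can move.** If size, or its logarithm, is normal, the median of 32 patients has a standard error of about √(π/2)/√32 = 1.253/5.657 = 0.22 SD.

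**Illustration with one factor.** Simulated trials used n = 32, about 30% events, one normal factor, and a likelihood-ratio test at two-sided 5%.

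| Effect per SD | Power, continuous | Power, median split |
|---|---|---|
| Odds ratio 2.0 | 38% | 26% |
| Odds ratio 2.5 | 58% | 40% |
| Log odds ratio 1.0 | 65.8% | 47.5% |
| Odds ratio 3.0 | 71% | 51% |

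With no effect, both tests rejected in about 6% of trials, so the gain is not bought with false positives.

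**The model as planned.** Counting baseline seizure activity as one term, the parameters are: baseline seizures 1, age 1, gender 1, grade 1, recurrence 1, IDH 1, MGMT 1, site 3, size 1, cortical involvement 1, surgery 2. The total is 14. Expected progressors are 32 × 0.30 = 9.6, or 9.6/14 = 0.7 per parameter. At a 10% rate they are 3.2, or 0.2 per parameter.

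This model was simulated with a true effect of one factor only and independent, evenly split categorical covariates (an assumption). Complete or quasi-complete separation, meaning no finite maximum-likelihood estimate, occurred in 81% of trials with age and size continuous and 78% with both cut. With a penalised fit, the factor was detected in 30% of trials when continuous and 23% when cut (two-sided 10% Wald level), a gain of 7 points.

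**The case against.** The strongest case on the other side has four parts.

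- **The model is exploratory.** No primary test, decision rule or sample size depends on these two terms. This stands and limits the point to a minor one.
- **The model is overloaded under either coding.** A reader might infer from the one-factor simulation that recoding gains nearly 20 points of power. The documents do not support that, because the planned model has eleven factors. Separation is about as common with either coding, and the gain under a penalised fit is far smaller. The one-factor figures show relative loss only.
- **The size of the loss is assumed.** It is tempting to say that about a third of the information on each factor is lost. That needs a roughly normal factor, a linear logit effect and a cut near the median, and the documents supply none of these. The age cut is fixed at 60 and acts as a median split only if the trial's median age is near 60. Hence the range.
- **Both cut rules are prespecified, and linearity is also an assumption.** Neither rule is chosen by looking at outcomes, and the cited earlier study may explain them, though it cannot be checked here. A linear term cannot be checked well with about 10 events. But prespecification does not recover lost information, and a step at a single value is also a strong assumption about shape.

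A reader might also infer that coarse groups leave confounding within them. That has not been shown here, and the single-arm model estimates no treatment effect that could be confounded.

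**Conclusion.** The point holds as a modest improvement to an exploratory secondary analysis. The article fixes both cuts, and neither saves a parameter. Assuming a linear logit effect, each cut loses roughly 25% to 55% of the information on its factor. The benchmark is 36% for a normal factor cut at its median, and the loss may be larger for a right-skewed size whose effect is linear on the raw scale. The size odds ratio refers to a threshold set by this sample; the age cut does not share that problem.

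The planned model's main limitation is about 14 parameters for about 10 expected progressors, and recoding does not cure it. The primary binomial test and the sample size are untouched.

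**What to change.** In the section on statistical methods for investigated endpoints, enter age (per 10 years) and tumor size (per cm, log-transformed if skewed) as single linear terms. Keep the two-group tables for description, and report the observed median size so that the grouping can be reproduced. Carry the same coding into the analyses of the separate components.

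The cost is a change of wording: no new data, parameters or patients. The downside is that linearity is assumed and can hardly be checked with about 10 events, which the report should say. The number of parameters is a separate matter that this change does not settle.

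### The joint prognostic logistic model has 14 slopes for about 10 expected events in 32 patients and is repeated for each component, so its adjusted odds ratios and Wald intervals would usually be infinite or uninformative

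*Protocol article*

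**What the plan says.** The section on statistical methods for investigated endpoints lists eleven candidate factors in a single logistic model. The list closes with "extent of surgery (no resection/biopsy only vs. subtotal resection vs. gross total resection) will be fitted to identify potentially relevant prognostic factors". The output is specified as "Adjusted odds ratios and 95% confidence interval", of Wald type. The article then states that "each component of the primary composite endpoint will be subjected to a separate statistical analysis using the same methods described above". The methods that precede that sentence are a point estimate with a 95% interval, a one-sided binomial test against 10%, and the logistic model. A further exploratory repeat is restricted to generalized seizures.

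The sample size section says "Thirty-two patients are required for the statistical analyses". It sets a background rate of 10% and an alternative of 30% for the rate of patients with progression. It gives no background rate for any single component.

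The methods section also calls the analysis as a whole descriptive and exploratory.

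**The concern.** The article fixes the model: one joint fit, mutual adjustment, ordinary odds ratios, Wald inference. With more coefficients than expected events, some combination of covariates will often split progressors from non-progressors perfectly or nearly so (complete or quasi-complete separation). The maximum-likelihood estimate is then not finite for at least one coefficient, and its Wald interval carries no information. Each component is a subset of the composite, so it cannot have more events and will usually have fewer.

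The component analyses also appear to inherit the 10% reference rate, which was chosen for the composite. At stake is the usefulness of the prognostic-factor and component results as hypotheses for the larger trial that the Discussion envisages.

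**Working it through.** **Plan's own figure.** Exact binomial, n = 32, null 10%, one-sided 2.5%: P(X ≥ 7 | 0.10) = 0.036 is too large and P(X ≥ 8 | 0.10) = 0.0117 is not, so the test rejects at 8 or more. Power P(X ≥ 8 | 0.30) = 78.8%, against 80% stated. With a 5% null it rejects at 5 or more (α = 0.0204) and power is 98.1%, against 98% stated. The design figures are reproduced.

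**Coefficients.** Nine factors contribute one each: baseline seizure activity, age, gender, grade, recurrence, IDH, MGMT, tumor size, cortical involvement. Tumor site (four levels) adds 3 and extent of surgery (three levels) adds 2. So 9 + 3 + 2 = 14 slopes, plus an intercept. Baseline seizure activity is counted as one term because its coding is not given.

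**Events per coefficient.** At 30%: 0.30 × 32 = 9.6 events, and 9.6 / 14 = 0.69. At 10%: 0.10 × 32 = 3.2 events, and 3.2 / 14 = 0.23.

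**Separation.** A linear-programming check was run on 600 simulated data sets per setting, with the outcome independent of all covariates. The Monte Carlo standard error near 65% is √(0.65 × 0.35 / 600), about 2 points. There were two assumed covariate patterns:

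- *Balanced*: all factors independent with equal category sizes.
- *Unbalanced*: 75% grade IV; IDH mutation 8% in grade IV and 65% in grade III; recurrence 20%; MGMT methylation 45%; cortical involvement 70%; uneven site and surgery categories. Baseline seizures of 21.5% (grade IV) and 48.8% (grade III) come from the Discussion. The other prevalences are assumptions.

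| Events | Balanced, n = 32 | Unbalanced, n = 32 |
|---|---|---|
| 3 | 100% | 100% |
| 5 | 99% | 99.5% |
| 8 | 83% | 91% |
| 10 | 65% | 79% |
| 12 | 49% | 68% |
| 16 | 36% | 61% |

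With all 35 patients evaluable and 10 events, the figures are 55% and 75%. Checks that drew the number of events at random gave about 80% in one assumed pattern at a 30% rate, and 49% to 59% at a 50% rate.

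**What Wald output looks like under separation.** Standard errors become very large. Among separated null data sets at a 30% rate, only about 2% to 7% showed any factor with p < 0.05, depending on the simulation set-up.

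**Component test against 10%.** It rejects at 8 or more of 32. The component rates below are assumptions.

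| True component rate | Against 10% (≥ 8) | Against 5% (≥ 5) |
|---|---|---|
| 15% | P(X ≥ 8) = 9.6% | P(X ≥ 5) = 53.6% |
| 20% | P(X ≥ 8) = 30.2% | P(X ≥ 5) = 79.6% |

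If a component's background rate were 10% itself, nothing would be lost.

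**The case against.** Five points can be made for the plan.

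- **The analysis is exploratory.** No decision rests on the model, and the primary test and sample size do not depend on it. This stands and limits the weight of the point. But the label governs how a result is read, not whether it can be estimated.
- **The full analysis plan may contain a fallback.** That is possible, and the article is not faulted for omitting one. The fault is in the joint Wald model that it does specify.
- **Failure is conditional.** This stands. The percentages depend on assumed prevalences, and the risk falls as progression becomes more common. With half the patients progressing it is about 50% to 60% in most settings, and 36% with perfectly balanced covariates.
- **The plan would not produce false prognostic factors.** A reader might infer that separation would fill the report with spurious factors. The planned Wald inference does not support that: under separation it rarely flags anything. The likely result is non-convergence or absurdly wide intervals.
- **The component null is inferred.** No sentence says that components are tested against 10%; it is the plain reading of the instruction to reuse the methods. A reader might infer that real component increases will be declared non-significant. That goes too far. A reference rate set too high is conservative, the loss depends on rates the article does not give, and an estimate with a 95% interval is planned alongside.

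**Conclusion.** The point holds as one about a secondary, exploratory analysis. The joint model has 14 slopes for about 9.6 expected events. At that number it has no finite maximum-likelihood solution in roughly 65% to 80% of data sets, under assumed prevalences and no true effects; true effects would make separation more likely. For a component with 3 to 5 events, failure is nearly certain (about 99% or more). The adjusted odds ratios and Wald intervals would therefore usually be infinite or uninformative, and the model cannot identify prognostic factors as intended.

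The test of components against 10% has no basis in the article, which sets that rate for the composite only. A component's background rate cannot exceed the composite's, and where it is lower the test loses power. The size of that loss is illustrative.

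**What to change.** Replace the joint maximum-likelihood model with Firth-penalised logistic regressions, one factor at a time, with profile-likelihood intervals. Allow at most one two-factor model, named before analysis and including baseline seizure activity.

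For each component, report the count, the rate and an exact 95% interval. Drop both the logistic model and the binomial test against 10%. Apply the same restriction to the generalized-seizure repeats.

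This changes analysis wording only and needs no more patients or data. The price is that fully mutually adjusted odds ratios are given up, and one-factor estimates may be confounded by related factors such as grade and IDH status. The report should say so.
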